## Abstract

**Introduction:**

Anterior cruciate ligament (ACL) tears are common in athletic and nonathletic populations, often resulting from activities involving rapid directional changes that place stress on the knee. Although advances in surgery and rehabilitation have improved recovery, many patients still struggle to regain pre-injury performance and face increased risk of re-injury. We hypothesize that combining standard rehabilitation with transcranial direct current stimulation (tDCS) may accelerate recovery, improve neuromuscular control, and strengthen key muscles like the hamstrings and hip abductors, reducing reinjury risk.

**Methods/materials:**

This randomized controlled trial protocol, approved by the Ethics Committee of the Catholic University of Valencia, follows a double-blind, comparative, longitudinal design per SPIRIT guidelines. Elite athletes will be randomized 1:1 into two age- and sex-matched groups: non-invasive brain stimulation (NIBS) + rehabilitation (ProtocolRHB) or sham NIBS + ProtocolRHB. The NIBS intervention uses tDCS to deliver low-intensity direct current to modulate cortical excitability. Data collection spans April 2025 to December 2027 with outcomes assessed at four postsurgical time points. The primary outcome is electromyographic (EMG) activity to evaluate muscle activation, crucial for restoring knee stability and function. Secondary outcomes include knee function (Lysholm Scale) and ACL-specific quality of life. EEG and TMS will assess cortical excitability and plasticity during voluntary muscle contraction.

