### Study design

2.1

This study will be a randomized controlled trial featuring a double-blind, comparative, and longitudinal approach. To ensure clarity and thoroughness, the study will adhere to the SPIRIT statement guidelines (Table 1) (37). The TIDieR checklist will be used to report outcomes (38). The planned investigation will include a protocol with two comparator arms: NIBS + ProtocolRHB and ShamNIBS + ProtocolRHB, with participants randomly assigned to either arm (Figure 1). Patients will provide written informed consent prior to any study procedure, including randomization. Data collection will be conducted between April 2025 and December 2027. This study was approved by the Ethics Committee of the Catholic University of Valencia (UCV/2023-2024/053). Additionally, the study was pre-registered at https://www.Clinicaltrial.gov on 01/01/2025 (NCT06818201).

**Table 1 T1:** Execution schedule – recruitment, intervention, and reassessment.

	Study period							
	Enrolment	Allocation	Post-allocation					Close-out
Time Point	*-t_1_*	0	*t_1_*	*t_2_*	*t_3_*	*t_4_*	*T_5_*	*t_x_*
Enrolment								
Eligibility screen	X							
Informed consent	X							
Allocation		X						
Interventions								
*[NIBS* *+* *_RHB_]*								
*[SHAM_NIBS_* + _RHB_*]*								
Assessments								
*[Anthropometric data]*	X	X						
*[Psychosocial Assessment]*			X	X	X	X	X.	X
*[Scoring Scale]*			X	X	X	X	X	X
*[Functionality]*					X	X	X	X
*[EGGTMS]*			X		X		X	X
*EMGs*			X		X		X	X

t1, 2024; 0, start study; t1, postsurgical; t2, postsurgical30; t3, postsurgical60; t4, postsurgical90; t5, postsurgical180; tx, study completion.

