### Randomization and blinding

2.5

A block randomization design with block sizes of 4 or 6 will be implemented to ensure an even distribution of participants across groups. A double-blind design will be employed, ensuring that both the patients and the evaluators collecting data on the study variables are blinded to the adjunctive effect of complementary tDCS during the rehabilitation. To assess blinding, one might apply the recommendations of Bang et al. (39, 40). We will implement a close-ended questionnaire to enquire participants and technicians about treatment assignment with the following questions:

Question 1: “What tDCS treatment do you believe you have received/applied?” The participants/technicians will be asked to choose from three possible answers: (1) real current, (2) simulated current, or (3) do not know. If participants or therapists answered Do not know’, then Question 2 was asked: “Please provide your best guess about the tDCS treatment you received/applied and asked to choose from two possible replies”: (1) real current; (2) simulated current. Finally, we will ask for a confidence assessment with Question 3: “For the tDCS treatment you chose in question 1 or 2, please provide on a scale of 0–10 the level of confidence you have in being correct, where 0 means you are totally guessing and 10 means you are completely sure”.

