### Sample size

2.6

The required sample size was determined using GPower® software (Franz Faul, Universität Kiel, Kiel, Germany), version 3.1.9.2. A preliminary sample of 46 subjects, divided into two groups of 23 participants each, was established for the intervention design. The primary variable (EMG output) was used for statistical analysis through repeated measures ANOVA. Cohen's effect size was set at 0.357 based on a previous study examining using surface EMG recordings as their primary outcome (41). The calculation incorporated a statistical power of 0.95, an alpha level of 0.05, and two intervention groups. To account for potential dropouts during treatment follow-up (estimated at 15%), an additional 3 participants were added to each group. This resulted in a total of 54 participants, with 27 per group. The chosen effect size, exceeding 0.357, is classified as “moderate” (42). If a greater percent of participants does not follow their planned treatment protocol (dropouts, non-adherence to treatment, or missing results), an “intention-to-treat” analysis will be conducted.

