##### Baseline characteristics

2.10.2.1

To evaluate demographic baseline measures across intervention groups, comparisons will be conducted using analysis of variance (ANOVA) or chi-square tests (i.e., NIBS + Protocol_RHB_ and ShamNIBS + Protocol_RHB_) to identify statistically significant differences between groups (*p* > 0.05).

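### The abstract calls the arms matched on age and sex, but the allocation described balances numbers only, and the baseline tests carry a reversed significance criterion

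*Protocol article*

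**What the plan says.** The Abstract (Methods/materials) gives balance on age and sex as a feature of the design: "Elite athletes will be randomized 1:1 into two age- and sex-matched groups".

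The body describes allocation in two places. Section 2.1 (Study design) describes two arms "with participants randomly assigned to either arm". Section 2.5 (Randomization and blinding) gives the method: "A block randomization design with block sizes of 4 or 6 will be implemented to ensure an even distribution of participants across groups". Neither section mentions age, sex, strata, minimisation or pairing.

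Section 2.10.2.1 (Baseline characteristics) says that for demographic measures "comparisons will be conducted using analysis of variance (ANOVA) or chi-square tests", and gives the purpose and criterion as to "identify statistically significant differences between groups (*p* > 0.05". Section 2.6 (Sample size) sets "a statistical power of 0.95, an alpha level of 0.05, and two intervention groups" and arrives at 54 participants, 27 per arm.

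Section 2.10.2.2 analyses primary and secondary outcomes by repeated measures ANOVA. The only between-subject factor it names is the experimental group. Section 2.8.1 lists sex and age among the recorded baseline data.

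**The concern.** Two statements are wrong as printed.

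- **The matching claim.** A reader of the abstract will take it that age and sex are balanced by construction. Permuted blocks constrain only the running count per arm. With 27 per arm, a visible chance difference in sex or age is an ordinary event, and the paper would then describe as matched two groups that are not.
- **The baseline criterion.** At an alpha of 0.05, a result is significant when p falls below 0.05. The printed inequality points the other way. Reversing it repairs the sentence but not the procedure: if allocation is properly random, every baseline difference is due to chance, so a significance test has no open question to answer.

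At stake are the accuracy of what the report may claim about comparability and, where age or sex is related to EMG activity, some precision in the group comparison.

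**Working it through.** **1. Claim and method side by side.** The Abstract asserts two groups matched on age and sex. Section 2.1 gives random assignment to two arms; section 2.5 gives blocks of 4 or 6. A block of 4 places two participants in each arm and a block of 6 places three, whatever their age or sex. The stated method therefore delivers equal numbers and nothing more.

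**2. Size of a chance sex imbalance.** Inputs: N = 54 with 27 per arm (section 2.6), and a male share of 58–73% (Introduction, for ACL tears in general). Using that share for this trial is an assumption: 0.58 × 54 = 31.3 and 0.73 × 54 = 39.4, so 31 to 39 men. With 27 per arm and sex unrelated to order of entry, the number of men X in one arm, given K men in all, is hypergeometric (54, K, 27). The difference between arms is |2X − K|.

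| Men in total (K) | P(difference ≥ 5) | P(difference ≥ 7) |
|---|---|---|
| 31 | 0.271 | 0.098 |
| 32 | 0.166 | 0.051 |
| 33 | 0.264 | 0.093 |
| 34 | 0.158 | 0.047 |
| 35 | 0.254 | 0.086 |
| 36 | 0.148 | 0.042 |
| 37 | 0.241 | 0.077 |
| 38 | 0.135 | 0.035 |
| 39 | 0.224 | 0.066 |

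The figures alternate because the difference has the same parity as K: with an even total, 5 or more in effect means 6 or more. The honest summary is the range, about 13–27% for 5 or more men and 3.5–10% for 7 or more.

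A simulation of the blocks themselves (20,000 runs per setting, N = 54) agrees. The share of women differed by 15 percentage points or more in 18% of runs with 27% women and in 22% with 42% women.

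**3. Size of a chance age imbalance.** The standardised mean difference has standard error √(2/27) = 0.272. P(|SMD| > 0.3) = 2 × [1 − Φ(0.3/0.272)] = 2 × [1 − Φ(1.10)] = 0.27. If ages were uniform over the eligible 16–35 years (assumption), the SD would be 19/√12 = 5.5 years, and a mean difference of 2 years or more occurred in about 18% of simulated runs.

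**4. The baseline criterion.** At alpha 0.05, about 5% of baseline comparisons give p < 0.05 under randomisation. Read literally, a rule that flags p > 0.05 would therefore label about 1 − 0.05 = 95% of them as different. With the sign corrected, the test is still no check of balance: among the simulated sex differences of 15 points or more, 70% (27% women) to 79% (42% women) were not significant by an uncorrected chi-square test.

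**The case against.** The strongest reply is that these are wording faults in a condensed article, and that it is easy to read too much into them. Most of that reply stands, and it limits the point in five ways.

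- **A reader might infer that the trial has no strata.** The article does not show that. It states none; a fuller protocol may contain them, and the abstract suggests that balance was intended. What remains is the mismatch between the abstract and the method the article does describe, down to block sizes. One of the two must change.
- **A reader might infer that the analysis leaves out age and sex.** A covariate list is commonly left to an analysis plan, which is not shown. The group-only description in section 2.10.2.2 is context here, not a separate fault.
- **A reader might infer that the baseline tests are the means of judging the matching.** Section 2.10.2.1 does not say so, and no later decision is tied to their result. The reversed sign may be a typing slip, or shorthand for calling the arms comparable when p exceeds 0.05. As printed it is still wrong, and step 4 of the working shows why the shorthand would not help.
- **A reader might infer that a sex imbalance would confound the EMG result.** The Introduction's figures on sex concern the incidence of ACL injury, and everyone enrolled already has a complete tear. The documents give no figure linking sex or age to EMG activity. Chance imbalance does not bias a randomised comparison on average, and its variability is already within the type I error. A constant sex difference in EMG level would also cancel from the group-by-time interaction, though not from the group main effect.
- **A reader might expect many false alarms from the baseline tests.** The number of tests is not stated. For k independent tests the chance of at least one is 1 − 0.95^k. If only sex, age and body mass index were tested, that is 14%.

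**Conclusion.** The point holds as two errors of statement. The abstract asserts matching on age and sex that the described allocation does not provide, and section 2.10.2.1 prints a significance criterion that is reversed against the trial's own alpha, for tests that serve no purpose under randomisation.

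The practical size is moderate. Roughly one trial in eight to one in four would show a difference of 5 or more men between arms. These figures assume 31 to 39 men among 54, exactly 27 per arm, allocation without strata, and sex unrelated to order of entry.

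The consequences are an inaccurate description of the groups and, to the extent that age or sex predicts EMG activity, some loss of precision. The documents do not support a conclusion that the treatment effect would be biased.

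**What to change.** 1. In the abstract, replace the matched wording with the allocation actually used. If strata exist in a fuller document, name them in section 2.5.
2. Prespecify sex and age as covariates in the primary model. Both are already collected (section 2.8.1). The cost is a few degrees of freedom. The gain depends on how strongly they predict EMG activity and falls mainly on the group main effect.
3. In section 2.10.2.1, report baseline data descriptively by arm, and delete the ANOVA and chi-square comparisons together with the p > 0.05 criterion. This costs only wording.
4. Optional, and only if enrolment is still early: stratify the block list by sex for participants not yet randomised. This needs a re-issued list and may leave one incomplete block per stratum. Data collection was scheduled from April 2025, so this may no longer be practical; items 1 to 3 are then sufficient.

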**Impact statement:**

This study integrates neurophysiology with rehabilitation, offering a novel approach to enhance functional recovery and lower reinjury risk post-ACL reconstruction, potentially informing future evidence-based sports medicine and neurorehabilitation strategies.

## Introduction

1

Anterior cruciate ligament (ACL) tears are common, especially among young and active individuals (1). For people aged 10–64 years, ACL injury incidence is estimated at 0.4–0.8 per 1, 000 person-years (2–4). An estimated 65%–75% of ACL tears occur during athletic activities, including soccer, handball, skiing, and basketball, which likely accounts for injuries occurring typically in young adults aged 28–35 years old (1, 2, 4–6). Nevertheless, a significant proportion of tears, approximately 25%–35%, occur in non-athletic settings (2). Most frequently, ACL tears occur in males, who account for 58%–73% of ACL tears (2, 4, 5, 7). However, despite males engaging in more high-risk activities, when data are adjusted for exposure frequency, females are 4–8 times more prone to ACL injuries (8–13). For both males and females, proper rehabilitation is crucial for recovery which enables approximately 80% of ACL reconstruction patients to resume some form of sports activity. However, only 65% of athletes who sustain an ACL tear and undergo successful traditional ACL reconstruction return to their pre-injury performance level, and even fewer (55%) return to competitive-level physical activity. In this context, surgical approaches that go beyond simple ACL repair for more functional ACL reconstruction are important. Injury- and surgery-related complications, such as graft failure (14), muscle injuries (15), osteoarthritis, and chondral and meniscal injuries (16, 17), may indirectly impact patient rehabilitation. A critical focus of physical therapy rehabilitation intervention is to strengthen and condition critical muscles to optimize knee stabilization (18).

Leg muscles play a critical role in stabilizing the knee, particularly after an ACL tear, and thus are vital in promoting recovery and preventing re-injury. Research has shown that the hamstrings and hip abductors are essential for minimizing the risk of relapse and addressing functional shortcomings following ACL procedures (19, 20). These muscles protect the knee by counteracting ACL strain as the reconstruction heals. The contribution of muscles to ACL stress and protection varies. Muscles such as the quadriceps and gastrocnemius have shown a higher contribution to ACL stress (21). In contrast, muscles such as the hamstrings, soleus, and gluteus medius have demonstrated a significant ability to counteract ACL strain, aiding in knee stability and injury prevention. Studies using kinematics, EMG, and motor cortex outputs have expanded our understanding of the muscular involvement in ACL injuries. The voluntary activation of the quadriceps in ACL-injured individuals has been studied using measures of cortical excitability. Previous studies have used various metrics, including the active motor threshold and cortical silent period (22), and tested muscles under low-intensity electrical stimulation conditions (23). Following ACL injury, substantial neural adaptations occur within the motor system, significantly affecting voluntary muscle activation and neuromuscular control. Evidence suggests that the cortical representation of leg muscles in the primary motor cortex undergoes reorganisation after ACL, leading to altered patterns of cortical excitability and impaired motor output (24, 25). These neuroplastic changes are particularly evident in the corticomotor pathways associated with the quadriceps, where reduced force-generating capacity is linked to modifications in both intracortical and corticospinal excitabilities (26). Such adaptations are believed to be fundamental for the restoration of motor function, with bidirectional plasticity playing a critical role in the reestablishment of musculoskeletal performance after surgery (27, 28).

While most previous research has focused on the spinal-level mechanisms of arthrogenic muscle inhibition (AMI), recent findings have highlighted broader central changes. These include increased reliance on the contralateral sensorimotor cortex during movement, heightened attentional demands during proprioceptive tasks, reduced somatosensory feedback, and altered corticospinal drive (24, 29–31). Conventional physiotherapy techniques, such as standard electrostimulation and “cushion crush” strategies, have shown limited efficacy in addressing neurophysiological deficits (32). However, novel approaches, such as targeted hamstring fatigue to inhibit the flexion reflex (33), peripheral interventions such as dry needling, and the immediate integration of active rehabilitation following cryotherapy, have demonstrated promising effects in reducing AMI and improving quadriceps function (34, 35). Standard rehabilitation programs often neglect to address sensorimotor alterations and deficiencies that arise following ACL injury and reconstruction. In recent years, noninvasive brain stimulation methods have been suggested as complementary approaches to exercise, aiming to elicit central responses that enhance neuromuscular control. The application of transcranial magnetic stimulation and transcranial direct current stimulation (tDCS) to the motor cortex has shown promising results in improving motor recovery (36). tDCS works by delivering a constant, low-intensity direct current through scalp electrodes to modulate cortical excitability, while TMS uses magnetic pulses to induce electrical currents that directly stimulate neuronal firing. These techniques differ in focality and mechanism, with tDCS modulating membrane potentials and TMS producing action potentials. This study will investigate the effects of combining tDCS with exercise-based rehabilitation targeting neuromuscular control and compare this intervention with sham tDCS alongside standard rehabilitation protocols. Our primary hypothesis is that decreasing cortical hyperexcitability in the motor area, when combined with exercise, will improve neuromuscular control, leading to better outcomes across the measured parameters and a lower risk of reinjury. Additionally, it is expected that the combination of tDCS and exercise-based rehabilitation will produce superior results compared to the rehabilitation and sham tDCS intervention.

## Material and methods

2

### Study design

2.1

This study will be a randomized controlled trial featuring a double-blind, comparative, and longitudinal approach. To ensure clarity and thoroughness, the study will adhere to the SPIRIT statement guidelines (Table 1) (37). The TIDieR checklist will be used to report outcomes (38). The planned investigation will include a protocol with two comparator arms: NIBS + ProtocolRHB and ShamNIBS + ProtocolRHB, with participants randomly assigned to either arm (Figure 1). Patients will provide written informed consent prior to any study procedure, including randomization. Data collection will be conducted between April 2025 and December 2027. This study was approved by the Ethics Committee of the Catholic University of Valencia (UCV/2023-2024/053). Additionally, the study was pre-registered at https://www.Clinicaltrial.gov on 01/01/2025 (NCT06818201).

**Table 1 T1:** Execution schedule – recruitment, intervention, and reassessment.

	Study period							
	Enrolment	Allocation	Post-allocation					Close-out
Time Point	*-t_1_*	0	*t_1_*	*t_2_*	*t_3_*	*t_4_*	*T_5_*	*t_x_*
Enrolment								
Eligibility screen	X							
Informed consent	X							
Allocation		X						
Interventions								
*[NIBS* *+* *_RHB_]*								
*[SHAM_NIBS_* + _RHB_*]*								
Assessments								
*[Anthropometric data]*	X	X						
*[Psychosocial Assessment]*			X	X	X	X	X.	X
*[Scoring Scale]*			X	X	X	X	X	X
*[Functionality]*					X	X	X	X
*[EGGTMS]*			X		X		X	X
*EMGs*			X		X		X	X

t1, 2024; 0, start study; t1, postsurgical; t2, postsurgical30; t3, postsurgical60; t4, postsurgical90; t5, postsurgical180; tx, study completion.

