### Procedure

2.4

After group assignment, all participants will be assessed at four scheduled time points after surgery: one month (post-surgical30), two months (post-surgical60), three months (post-surgical90), and six months (post-surgical180). Scoring scales and psychosocial assessments will be evaluated at each visit (Figure 1). All assessments will be conducted bilaterally to allow within-subject comparisons.

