	PHASE 2.2	9–12		• Absence of instability episodes • 10 SLS at 60° • Functional evaluation • Quadriceps index >80% • Hamstring index >80% • Gluteus medius >80%	Previous phase + • Bilateral plyometrics in partial load • Bilateral plyometrics in full load • Submaximal training in sport-specific sagittal plane movements
Running, agility, and landings	PHASE 3.1	12–16	• Attain optimal performance in jump exercises • Complete the prescribed plyometric, agility, and running program • Regain full strength and balance capabilities	• Achieve pain-free and inflammation-free running • Functional evaluation • Quadriceps/hamstring/Gluteus medius strength >90% • Q/H RATIO >66% • Hop test >90%	Exercises (continue progressive strength training + plyometric, agility, and running block). • Bilateral sagittal plane plyometrics: broad jump, box jump, tuck jump, hop over line. • Unilateral sagittal plane plyometrics: pogo hops, lunge jump, bounding run. • Sagittal plane agility: ladder drills, forward and backward, figure-eight, deceleration, etc. • Running: adaptation protocol + running protocol (week 1)
	PHASE 3.2	16–24		• Absence of pain or inflammation • Pain-free activity performance • Appropriate movement pattern execution	Exercises (continue progressive strength training + plyometric, agility, and running block). • Frontal plane bilateral plyometrics: lateral hop over the line/hurdles, tuck jumps over the line/hurdles, etc. • Frontal plane unilateral plyometrics: lateral hop over the line/hurdles, tuck jumps over the line/hurdles, etc. • Frontal plane agility: zig-zag run, side shuffle/shuffle run, cone drills, crossover step, lateral ladder drills. • Running: running protocol (weeks 2–7).
Return to play	PHASE 4	+24	• Melbourne Return to Sport Score of 95+ • Patient demonstrates comfort, confidence, and readiness to return to sports • ACL injury prevention program implemented	• Functional evaluation • Quadriceps/hamstrings/gluteus medius strength index >90% • Q/H RATIO >70% • Hop test >90% RTP • Month 7: unrestricted training • Month 9/10 return to competition • Functional evaluation: • Quadriceps/hamstrings/gluteus medius strength index >95% • Q/H RATIO >75% • Hop test >95%	• Exercises (continue progressing strength block + plyometrics and multiple agility) • Multiple plyometrics: drop jump + rapid change of direction, 90° and 180° jumps, etc. • Multiple agility: box and start drill, lateral shuffle over the hurdles, etc.

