##### Functional assessment

2.8.3.2

Functional Jump Tests are commonly used to evaluate patients after ACL repair, especially to assess the Limb Symmetry Index (LSI) (56, 57). The current literature suggests that the normal LSI is >90% when comparing the ACL-reconstructed limb with the non-operated limb (58). Functional Jump Tests are also cost-effective and simple to assess, as they do not require extensive space or equipment, enabling the evaluation of knee functional capacity and offering a measurable metric that can be tracked over time. Ebert et al. identified eight jump tests—single hop for distance, 6 m timed hop, triple hop for distance, triple crossover hop for distance, single medial hop for distance, single lateral hop for distance, single limb countermovement jump for height, and timed speedy hop test—that were the most effective in highlighting functional limb asymmetries in patients post-ACL injury (59).

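### Table 1 schedules single-leg jump tests at day 60, before Table 2 introduces single-leg jumping; at day 90 the two tables conflict only under conditions

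*Protocol article*

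**What the plan says.** **Timing of the tests.** In section 2.1, the Table 1 row "Functionality" is marked at t3, t4, T5 and tx and is blank at t1 and t2. The key gives "t1, postsurgical; t2, postsurgical30; t3, postsurgical60; t4, postsurgical90; t5, postsurgical180; tx, study completion". Section 2.4 repeats these visits as two, three and six months after surgery.

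**Content of the tests.** Section 2.8.3.2 describes the functional assessment only as jump tests, used to obtain the Limb Symmetry Index of the reconstructed against the non-operated limb. It lists eight tests that a cited study found most informative. They begin with "single hop for distance, 6 m timed hop, triple hop for distance, triple crossover hop for distance" and include medial and lateral hops. The article does not say which of the eight will be performed.

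**Rehabilitation content.** Table 2 (section 2.7.1) lists no jumping in Phase 2.1 (weeks 6–8). Phase 2.2 (weeks 9–12) adds "Bilateral plyometrics in partial load" and then the same in full load. Phase 3.1 (weeks 12–16) adds "Unilateral sagittal plane plyometrics: pogo hops, lunge jump, bounding run" and is the first phase with a hop test (>90%) among its criteria. Phase 3.2 (weeks 16–24) adds "Frontal plane unilateral plyometrics: lateral hop over the line/hurdles". Section 2.7.1 makes advancement between phases depend on criteria, not on time alone.

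**Analysis.** Section 2.10.2.2 applies repeated measures ANOVA to primary and secondary outcomes, with time, group and interaction effects.

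**The concern.** A limb symmetry score needs each leg to be tested alone. Table 1 therefore asks for single-leg jumps on the operated leg at a date when Table 2 has not yet brought that movement into rehabilitation. An assessor at the day-60 visit cannot tell from the article whether to run the tests.

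The statistical consequence depends on how sites resolve this. If only participants who have progressed far enough are tested, having a jump value at an early visit becomes a result that arises after randomisation. Better neuromuscular control is what tDCS is hypothesised to produce, so progression, and with it the chance of being tested, could differ by arm. The early comparison would then set selected subsets against each other. A repeated measures ANOVA that needs a value at every time level would also remove the untested participants from the day-180 comparison, where their data may be complete.

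**Working it through.** The article states no figure to reproduce. The check converts visit days to weeks and compares them with the phase windows.

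**Inputs.** Visit days 60, 90 and 180 (Table 1). Single-leg jumping from week 12 and frontal-plane jumping from week 16 (Table 2). The running, agility and landing phase from week 13 (text of section 2.7.1).

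**Visit day to elapsed weeks (day ÷ 7).** 60/7 = 8.57; 90/7 = 12.86; 180/7 = 25.71.

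**First day of week w.** The article does not say how weeks are counted, so both readings are shown. In elapsed weeks, week w starts on day 7w. Counting the first seven days as week 1, it starts on day 7(w − 1) + 1.

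| Start | Elapsed | Counted from week 1 |
|---|---|---|
| Week 12 (Phase 3.1, Table 2) | day 84 | day 78 |
| Week 13 (third phase, text) | day 91 | day 85 |
| Week 16 (Phase 3.2) | day 112 | day 106 |

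**Day 60.** It falls at the end of Phase 2.1 or the start of Phase 2.2, depending on the reading. Neither phase lists single-leg jumping. The gap to Phase 3.1 is 84 − 60 = 24 or 78 − 60 = 18 days. The order is the same on every reading and does not depend on which jump tests are chosen.

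**Day 90, sagittal tests.** By Table 2, Phase 3.1 began 90 − 84 = 6 or 90 − 78 = 12 days earlier, so single-leg sagittal jumping has nominally started. By the week-13 start in the text, day 90 is one day short (day 91) or five days in (90 − 85). There is no material conflict for a participant on the nominal schedule. One who has not met the criteria would still be in Phase 2.2, which lists bilateral plyometrics only.

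**Day 90, crossover, medial and lateral hops.** Frontal-plane jumping starts 112 − 90 = 22 or 106 − 90 = 16 days later. The conflict exists if these tests are used.

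**Day 180.** At week 25.7 the visit lies after the nominal end of Phase 3.2 (week 24), so all listed tests fit both tables for a participant on schedule. A slower participant may still be behind.

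**Consequence for the ANOVA.** If testing waited for Phase 3.1, the day-60 level would be empty for everyone on the nominal schedule. At day 90 it would be filled only for those who had progressed. Complete-case handling across time levels carries both gaps forward to day 180.

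**The case against.** The strongest reply is that Table 2 governs training, not testing. Its column gives recommended exercises and it states no ban on assessments. Phase 2.2 already lists a functional evaluation, and section 2.4 says that all participants are assessed at the scheduled visits. This stands in part: a reader might infer that early testing is unsafe or breaks a loading rule, and the article supports neither. It does not remove the day-60 mismatch. The other criteria in Phase 2.2 include single-leg squats and strength indices but no hop test, and Table 2 first names a hop test in Phase 3.1.

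A second reply is that the article does not commit to all eight tests, and that the full protocol may assign tests to visits. This stands for day 90, where a sagittal test such as the single hop fits Phase 3.1. It does not help at day 60, because limb symmetry on any jump test requires single-leg performance.

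A third reply is that nothing says testing is restricted to participants judged ready. That is correct. Selective missingness is a plausible consequence of the conflict, not something the plan prescribes.

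**Conclusion.** The conflict at day 60 is established. Table 1 calls for single-leg jump tests 18 to 24 days before Table 2 introduces single-leg jumping, whichever tests are chosen. At day 90 it is conditional on using crossover, medial or lateral hops, or on a participant not having reached Phase 3.1. A reader might infer that both early visits conflict outright; the Phase 3.1 window does not support that.

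The risk to the analysis rests on two assumptions: that sites would limit early testing to those who have progressed, and that the ANOVA is run on participants with every time level. Under these, missingness could be related to arm, and day-180 data would be lost. A reader might want a size for the resulting bias. None can be derived, because the article gives no attempt rates and no spread for limb symmetry.

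Severity is moderate. The functional tests are a secondary outcome, and neither the EMG primary outcome nor the sample size is affected.

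**What to change.** 1. The clinical team should reconcile Table 1 (section 2.1), Table 2 (section 2.7.1) and section 2.8.3.2, and state which functional tests apply at which visit. Which of these governs is theirs to decide.
2. In section 2.10.2.2, state that a participant does not need earlier jump-test values to enter the day-180 limb symmetry comparison.
3. At any earlier visit where a jump test is scheduled, record tests not attempted, with the reason, and report them by arm, not as ordinary missing values.

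The cost is an edit to the tables, a sentence or two of analysis text and one extra field on the assessment form. The downside is that early jump-test comparisons become weaker or are lost. Item 3 should also apply at day 180, since a slow participant may not be ready even then.
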